## Data Safety Monitoring Plan (DSMP)

Data safety Monitoring will be rigorously performed throughout the study. All forms will be reviewed again by the study physician after enrolment and data collection followed by a supervisor for completeness, legibility, and internal consistency. A supervisor will perform random checks to ensure the validity of collected data by the study physician. The study physician will be trained accordingly for patient screening; enrolment, data collection, and study participants follow-up before initiation of the study according to rigorously standardized operating procedures (SOPs).

The study will be performed in compliance with the ‘Declaration of Helsinki’ (2000), the International Council of Harmonization (ICH), Tripartite Guidelines, Guideline for Good Clinical Practice (GCP). These procedures ensure the protection of the rights and the integrity of the study participants, adequate and correct conduct of all study procedures, adequate data collection, adequate documentation, and adequate data verification.

## Ethical Assurance for Protection of Human rights

The study protocol and data collection tools, and the informed consent forms to be used in the study will be submitted to the Research Review Committee (RRC) and the Ethical Review Committee (ERC) of icddr, b, and the study would be initiated only after receiving approval of the ERC. Before enrollment signed informed consent will be obtained from the parents/guardians of the children. The risk of enrolled subjects from participation in the study is minimal. Administration of L-carnitine and placebo supplements will be done with informed written consent. Patients will receive routine medical care. Adverse medical events are not anticipated from the routine procedures involved in the study. However, if any adverse events or injuries occur, providers will manage such events according to routine practice. The Ethical Review Committee of icddr, b will be notified of any serious adverse events (death, any life-threatening condition that requires ventilator/oxygen support, permanent damage or disability) and deviations from the protocol. Moreover, participation in this study is voluntary. Refusal to take part in the study will involve no breach in the continuity of care and the child will receive the standard treatment of this hospital. The study participants have the right to withdraw at any time from the study and also have the right to refuse to answer any question. Privacy, anonymity, and confidentiality of data/information identifying the child will strictly be maintained. We would keep all medical information, description of treatment, and results of the laboratory tests performed confidential, under lock and key, and none other than our research staff will have an access to this information.

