**Eligibility Criteria**

Inclusion criteria

- Diarrheal children with SAM aged 9-24 months
- Signed informed consent by the guardian/caregivers

Exclusion criteria

- Severe sepsis or Septic shock
- Patients already taking medications containing L- carnitine
- Children with Tuberculosis
- Children with congenital defects or chromosomal anomalies
- Children with a diagnosed case of Thalassemia
- Children with an active or previous history of convulsion

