**Management**

Children will be given their first dose of supplementation when they would be considered improved, i.e. no diarrhea for last 24 hours, patient fulfill the criteria of NRU transfer (presence of oedema, or/and WLZ <-3SD, or/and WAZ <-4SD). At NRU after randomization trained research staff will observe each child for 60 minutes following ingestion of investigational product and record any adverse event- nausea, vomiting etc. Vomiting is defined as the forceful emptying of stomach contents and will be recorded if it happened within 60 minutes following the administration of investigational product. Children will get supplementation of investigational product in addition to standard of care at NRU for 15 days. Supplementation will be given at every 8 hours under supervision of a trained staff.

**Study Days**Patients will be followed up every day by a study physician at NRU for 15 days. Adverse events will be documented and drug accountability recorded. During this intervention period if study participants fulfill the discharge criteria of NRU (WLZ/WHZ ≥ -2SD, WAZ ≥ -3SD and oedema resolved), we will discharge the patient with remaining dose of the syrup and advise them to come for follow up into after completion of the remaining dose. This same method will be applicable for both the intervention arm and placebo arm.

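### The serious adverse event rule notifies the ERC of a life-threatening event only if it needs a ventilator or oxygen, and omits readmission and prolonged stay

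*Protocol*

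**What the plan says.** The rule stands in the protocol under Ethical Assurance for Protection of Human rights. The ERC is to be notified of "serious adverse events (death, any life-threatening condition that requires ventilator/oxygen support, permanent damage or disability", "and deviations from the protocol". For everything else the same section says that "if any adverse events or injuries occur, providers will manage such events according to routine practice".

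Other safety statements in the protocol:

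- **Management (including Study Days).** A study physician sees each child daily at the NRU for 15 days, and "Adverse events will be documented and drug accountability recorded". A child who meets the discharge criteria before day 15 leaves early: "we will discharge the patient with remaining dose of the syrup". The ERC Abstract Summary, under Time required, says the same.
- **Safety Plan.** Gastrointestinal symptoms and fever are named as the most likely events. Adverse events are summarised descriptively, and the safety population is every child who took at least one dose.
- **Data Safety Monitoring Plan.** Forms are checked for completeness, legibility and consistency. A general commitment follows: "The study will be performed in compliance with the ‘Declaration of Helsinki’ (2000", with ICH and GCP named in the same sentence.
- **Eligibility Criteria.** Exclusions include "Severe sepsis or Septic shock" and "Children with an active or previous history of convulsion".

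**The concern.** The second item in the bracket makes seriousness depend on one form of support rather than on the threat to life. Two children with equally dangerous events would be classified differently according to whether oxygen was used. The list also has no item for readmission or prolonged stay.

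This matters because ERC notification is the only outside safety oversight that the protocol describes. The participants are severely malnourished children aged 9 to 24 months, some of whom will take part of the course at home. The same section calls the risk of participation minimal. A trigger that misses some life-threatening events and all uncomplicated readmissions gives the committee an incomplete basis for judging whether that holds.

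**Working it through.** No arithmetic decides this point. The check is to read the rule literally, run plausible events through it, and look for any other text that widens it.

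**1. Is the list open or closed?** The bracket contains no wording that marks its items as examples, and no item for other medically important events. It reads as the definition: (a) death, (b) a life-threatening condition needing a ventilator or oxygen, (c) permanent damage or disability.

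**2. Events run through the list.**

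- Shock treated with oxygen: meets (b), notified.
- Convulsion that leaves permanent damage: meets (c), notified.
- Life-threatening convulsion, shock or severe dehydration managed without oxygen or a ventilator, with full recovery: meets none, not notified.
- Readmission after early discharge, without oxygen, with full recovery: meets none, not notified.
- Adverse event that only prolongs the NRU stay: meets none, not notified.

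**3. Are such events foreseeable in this trial?** Diarrhoea is among the most likely adverse events in the Safety Plan, so dehydration is a fair inference. The Project Summary and the Background say that severe malnutrition has high relapse rates after discharge. Management allows discharge on study syrup, so readmission during treatment can occur.

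**4. Does other text widen the trigger?**

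- Management provides for recording, and ties it to daily follow-up at the NRU.
- The Safety Plan provides for a descriptive summary.
- The Data Safety Monitoring Plan checks forms.
- The ICH/GCP commitment reproduces no seriousness definition.
- The appended Declaration of Helsinki (paragraph 23) asks that the committee be informed of any serious adverse events, but does not define the term.

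None of these adds an event to the list.

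**5. Where is the gap widest?** In the NRU a physician sees the child daily. After early discharge, the planned contacts (Management, Drug accountability, Anthropometric measurements) are:

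- the follow-up when the remaining doses are finished, about day 15;
- a telephone call 15 days after completion: 15 + 15 = about day 30;
- a measurement 180 days after completion: 15 + 180 = about day 195.

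The rule does not say whether it applies to days at home or until when.

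**The case against.** The strongest reply is that nothing is lost. Adverse events of any type are documented during the NRU stay and summarised for every dosed child, so an in-hospital convulsion would appear in the safety data whatever its label. That stands. A reader might infer that these events go unrecorded, and the documents do not support that.

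A reader might also infer that convulsions and shock as such escape reporting. They do not: any life-threatening case given oxygen, and any ending in death or permanent damage, is already notifiable.

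Three further inferences go too far:

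- **An understated serious-event comparison by arm.** The protocol plans no such count. Its adverse event summary does not depend on seriousness.
- **A proven contradiction of GCP.** The protocol reproduces no GCP definition. The general commitment could be read as supplementing the list. What can be said is that the two passages need reconciling, because staff will apply the explicit list.
- **Exclusions chosen because the product is thought to cause these events.** The Eligibility Criteria give no reasons. They show only that such events are relevant to this population.

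The Appendix 3 questionnaires are not in the text on which this point rests, so an event form there cannot be ruled out. A form would not change the wording of the notification rule.

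**Conclusion.** The concern holds as a defect in a stated rule. Followed literally, the rule leaves two groups of events without ERC notification: life-threatening events managed without oxygen or a ventilator that cause neither death nor permanent damage, and readmissions or prolonged stays that meet no listed item. The gap lies in classification as serious and in notification, not in recording at the NRU.

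Its size cannot be put as a number. The rule applies to all 98 planned children, but the protocol gives no rate for these events and none should be assumed.

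The conclusion rests on reading the bracket as the full definition, which its wording supports, and on no other rule in force widening it. It should be fixed because it concerns participant protection and the change is cheap. It does not affect randomisation, the primary outcome or its analysis.

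**What to change.** In Ethical Assurance for Protection of Human rights, reword the bracket so that serious adverse events are: death; any life-threatening event, whatever support it needs; readmission to hospital; prolongation of the stay because of an adverse event; and permanent damage or disability. Because the stay also depends on the NRU discharge criteria, the study physician should record whether an adverse event caused the prolongation.

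State that the rule applies from the first dose, including doses taken at home. Later events can be asked about at the telephone call and the 180-day measurement already planned. These contacts are 180 − 15 = 165 days apart, so events between them will be captured late and from recall; the protocol should say so. Add a sentence reconciling the list with the ICH/GCP commitment in the Data Safety Monitoring Plan.

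The cost is a revised sentence, a question at contacts already planned, a few more ERC notifications and a less favourable-looking serious-event tally. No change to treatment is involved.

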**Timeline**

|  | ***Study Timeline***  (October'2021 - September'2022) | | | | | | |  |  |  |  |  |  |
| --- | --- | --- | --- | --- | --- | --- | --- | --- | --- | --- | --- | --- | --- |
| **Study Proceedings** | Oct | | Nov | Dec | Jan | Feb | Mar | Apr | May | June | July | Aug | Sep |
| Staff recruitment, training and orientation |  |  |  |  |  |  |  |  |  |  |  |  |  |
| Patient enrollment and data collection |  |  |  |  |  |  |  |  |  |  |  |  |  |
| Intervention |  |  |  |  |  |  |  |  |  |  |  |  |  |
| Laboratory Assessment |  |  |  |  |  |  |  |  |  |  |  |  |  |
| Data entry, cleaning and data preparation for analysis |  | |  |  |  |  |  |  |  |  |  |  |  |
| Data analysis and interpretations |  | |  |  |  |  |  |  |  |  |  |  |  |
| Report writing and preparation of manuscript |  | |  |  |  |  |  |  |  |  |  |  |  |

## Use of Animals

| Not applicable |
| --- |

##

## Collaborative Arrangements

| Not applicable. |
| --- |

## Facilities Available

The study will be conducted at the Dhaka Hospital of the International Centre for Diarrhoeal Disease Research, Bangladesh (icddr,b). This hospital is located in Dhaka city, the capital of Bangladesh. The vast majority of the patients come from poor socio-economic backgrounds from urban and peri-urban Dhaka, Bangladesh. This hospital has a separate ward including a nutrition rehabilitation ward, well-equipped laboratory facilities capable of performing all the clinical tests, and also has an Intensive Care Unit (ICU), equipped with mechanical ventilation and other facilities for the management of a critically ill patient. The hospital has a long track record of conducting clinical trials and other studies, some of which are known globally for contributing to improved health and nutrition of infants and young children.

**Anticipated results/outputs**

This study will facilitate us to evaluate the role of carnitine supplementation in the rate of weight gain and duration of hospital stay in children who are severely malnourished and received inpatient treatment. The knowledge on carnitine status as well as the prevalence of carnitine deficiencies at enrolment in children with severe acute malnutrition will help us to design a better treatment strategy in this vulnerable group of population.

**Potential Impact**

In addition to standard of care judicial use of the L-carnitine oral solution will be recommended if the study shows that L-carnitine supplementation increases the rate of weight gain and also affects the duration of hospital stay as well as EED biomarkers of SAM children.

# Budget

**Detailed Budget for the study titled:** Role of L-Carnitine supplementation on rate of weight gain and biomarkers of Environmental Enteric Dysfunction (EED) in children with severe acute malnutrition

**Name of Principal Investigator:** [name]

**Protocol Number:** PR-21046

**Division:** Nutrition and Clinical Services Division (NCSD)

**Funding Source:** icddr,b (Rainy Day Fund)

**Budget:** Direct: US$ 25,000; Indirect: 00% US$; Total: US$ 25,000

**Study period:**  From: October'21 to September'22

**Strategic Priority Code(s):**

| **Project Title:** | | Role of L-Carnitine supplementation on rate of weight gain and biomarkers of  Environmental Enteric Dysfunction (EED) in children with severe acute malnutrition | | | | | | | |  | |
| --- | --- | --- | --- | --- | --- | --- | --- | --- | --- | --- | --- |
| **Donor Name:** | | icddr,b | | | | | | | |  | |
| **Budget Period:** | | October'21 - September'22 | | | | | | | |  | |
| **PI Name and Email:** | | [name], [contact] | | | | | | | |  | |
| **Total Budget** | | 25,000 | |  | | | | | |  | |
|  | **Cost Categories** | | **Grade/ Step** | **Effort**  **(%)** | **No of**  **Staff** | **No. of months** | **Rate/m onth ($)** | **Year-1** | **Year-2** | | **Total**  **2021 to**  **2022**  **USD** |
|  | **Oct to**  **Dec 2021**  **USD** | **Jan to**  **Sep 2022**  **USD** | |
|  | **Personnel** | | | |  |  | |  |  | |  |
|  | [name] (PI) | | Project Research Physician (Unclassified) | 50% | 1 | 8 | 702 | 1,053 | 1,931 | | 2,984 |
|  | Field Research Assistant | | GS3 (CSA) | 100% | 1 | 12 | 469 | 1,407 | 4,643 | | 6,050 |
|  | Health Worker/Field Attendant | | GS1 (CSA) | 100% | 1 | 12 | 353 | 1,059 | 3,495 | | 4,554 |
|  | **Sub-total** | | | |  |  |  | **3,519** | **10,068** | | **13,587** |
|  | **Equipment, Material and Supplies** | | | |  | **Qty** | **Rate** |  |  | |  |
|  | Supplies (Stock and Non-Stock items) | | | |  |  |  | 200 | 100 | | 300 |
|  | Laboratory Supplies (Reagents and Kits for testing L-carnitine and biomarkers of EED) | | | |  |  |  | 5,000 | 5,000 | | 10,000 |
|  | **Sub-total** | | | |  |  |  | **5,200** | **5,100** | | **10,300** |
|  | **Printing & Publications** | | | |  | **Qty** | **Rate** |  |  | |  |
|  | Printing & Photocopy | | | |  |  |  | 23 | 40 | | 63 |
|  | **Sub-total** | | | |  |  |  | **23** | **40** | | **63** |
|  | **Other Direct Costs** | | | | **Unit** | **Qty** | **Rate** |  |  | |  |
|  | Intervention Drug and Placebo | | | |  |  |  | 150 |  | | 150 |
|  | Laboratory & diagnostic tests, drugs and treatment of children with SAM | | | |  |  |  | 450 | 450 | | 900 |
|  | **Sub-total** | | | |  |  |  | **600** | **450** | | **1,050** |
|  |  | | | |  |  | |  |  | |  |
|  | **Total Direct costs** | | | |  |  | | **9,342** | **15,658** | | **25,000** |
|  | **IndirectCosts/Overhead** | | | |  |  | | - | - | | - |
|  | **Total Costs** | | | |  |  | | **9,342** | **15,658** | | **25,000** |

**Budget Justifications:**

| **Project Title:** | Role of L-Carnitine supplementation on rate of weight gain and biomarkers of Environmental Enteric Dysfunction (EED) in children with severe acute malnutrition |
| --- | --- |
| **Donor Name:** | icddr,b |
| **Budget Period:** | October'21 - September'22 |
| **PI Name and Email:** | [name], [contact] |
| **Budget elements** | **Justification** |
| **Personnel** | The proposed study activities include screening and enrollment of study participants, data collection, anthropometry, physical follow-ups and laboratory assays of enrolled participants. A substantial portion of the costs (Total $13,587) will be incurred for salary purpose as well as economic expenses of PI and study staff. |
| **Equipment, Material and Supplies** | A total cost of $10,300 will be incurred for purchasing study materials as well as laboratory kits and reagents. |
| **Printing & Publications** | A total cost of $63 will cover the photocopy of study materials |
| **Other Direct Costs** | A substantial amount of total $1,050 will be incurred for laboratory and diagnostic tests of the children, and for purchasing intervention drugs and placebo. |
| **Indirect Costs/Overhead** | **0% overhead cost** |

#

# Other Support

| Not Applicable. |
| --- |

**Appendix 1**

**External Reviewer: 1**

Page 1 of 2

**Title:** Role of L-Carnitine supplementation on rate of weight gain and biomarkers of Environmental Enteric Dysfunction (EED) in children with severe acute malnutrition

Summary of Referee’s Opinions: Please see the following table to evaluate the various aspects of the proposal by checking the appropriate boxes. Your detailed comments are sought on a separate, attached page.

|  | Rank Score | | |
| --- | --- | --- | --- |
|  | High | Medium | Low |
| Quality of project | X |  |  |
| Adequacy of project design | X |  |  |
| Suitability of methodology | X |  |  |
| Feasibility within time period | X |  |  |
| Appropriateness of budget | X |  |  |
| Potential value of field of knowledge | X |  |  |

### Detailed Comments

Please briefly provide your opinions of this proposal, giving special attention to the originality and feasibility of the project, its potential for providing new knowledge and the justification of financial support sought; include suggestions for modifications (scientific or financial) where you feel they are justified. (Use additional pages if necessary)

**Title:** Role of L-Carnitine supplementation on rate of weight gain and biomarkers of Environmental Enteric Dysfunction (EED) in children with severe acute malnutrition

**PI:** [name]

**Reviewer**: [name]

[name] and colleagues are seeking to fill a crucial knowledge gap in the field of malnutrition and EED by performing a clinical trial of Levocarnitine for the treatment of severe acute malnutrition and EED. The trial is a well-designed randomized placebo-controlled double blinded trial. In addition block randomization will be used which may help to decrease bias given the smaller sample size. There is sufficient background data to suggest Levocarnitine’s utility in treating EED and malnutrition and thus, such a trial is scientifically warranted. The biomarkers of EED selected are broad, encompassing enteric inflammation, systemic inflammation, and intestinal integrity. The analysis plan is reasonable although authors should clearly state an adjusted model will also be created and describe the covariates included (or how they will be selected). The intervention is relatively benign when taken PO. The safety plan seems adequate for this small trial given the side effect profile of the intervention (i.e. generally do not see the cardiac effects when given PO).

Investigators plan to use a standard dose of 100mg/kg/day. However, literature supports titration to higher doses in certain children. It is unknown exactly how deficient children with SAM and EED are and thus it may be that this dose is insufficient to replete some children. Correction for baseline carnitine levels may be indicated in the final analysis but understanding the distribution of those baseline levels will also be a valuable addition to our current knowledge. In terms of the secondary outcome of study of Levocarnitine’s effect on EED, the interval of 15 days may be too short to recognize an effect on certain biomarkers. Specifically, those of gut permeability may take longer to correct. Also, the degree of baseline elevation in inflammatory biomarkers (including enteric inflammation) may be dependent on the type of pathogen causing the diarrhea that led to the child’s admission. Children with secretory diarrhea will have less elevation than those with inflammatory pathogens such as Campylobacter or Shigella. Inflammatory biomarkers to these pathogens may decrease regardless of intervention as the infection clears although likely will not normalize. One way to create a more heterogenous group without expensive pathogen testing would be to exclude children with fecal RBC positivity. Although pathogens such as Campylobacter are increasingly being recognized causing non-bloody diarrhea in addition to the more classic bloody diarrhea, this may help in excluding children with the highest levels of colitis (i.e. those that would lead to fecal RBC testing being positive). Alternatively, if the budget allows, fecal pathogen testing could be arranged and only children with viral disease enrolled as it would be expected that viral pathogens change the inflammatory biomarkers to a lesser degree. Of course, co-pathogen carriage may make screening difficult. Finally, there is evidence that the enteric microbiota plays an important role in carnitine metabolism. While likely beyond the scope of this project and budget, it would be reasonable to bank a separate aliquot of stool for the purpose of future microbiome studies. If this trial does demonstrate an effect in the treatment group, external funding for this line of question could potentially be secured. This should be a separate aliquot to limit freeze-thaw cycles and be stored in RNase/DNase free cryovials at -80oC.

Response to External Reviewer’s comments:

Reviewer: [name]

Comment: “[name] and colleagues are seeking to fill a crucial knowledge gap in the field of malnutrition and EED by performing a clinical trial of Levocarnitine for the treatment of severe acute malnutrition and EED. The trial is a well-designed randomized placebo-controlled double blinded trial. In addition, block randomization will be used which may help to decrease bias given the smaller sample size. There is sufficient background data to suggest Levocarnitine’s utility in treating EED and malnutrition and thus, such a trial is scientifically warranted. The biomarkers of EED selected are broad, encompassing enteric inflammation, systemic inflammation, and intestinal integrity. The analysis plan is reasonable although authors should clearly state an adjusted model will also be created and describe the covariates included (or how they will be selected). The intervention is relatively benign when taken PO. The safety plan seems adequate for this small trial given the side effect profile of the intervention (i.e. generally do not see the cardiac effects when given PO).”

Response: Thank you very much for your comments and considerations.

Comment: “Investigators plan to use a standard dose of 100mg/kg/day. However, literature supports titration to higher doses in certain children.”

Response: Thank you so much for your opinion. We agree with you regarding evidence on titration. However, slow administration of the dose is also evident. Therefore, we will give the supplementation of oral solution slowly to our study participant as per guidance of published literature.

Comment: “It is unknown exactly how deficient children with SAM and EED are and thus it may be that this dose is insufficient to replete some children.”

Response: Dear reviewer, thank you for your valuable suggestion. In previous study on carnitine supplementation in SAM children they gave supplementation of 100 mg/kg/day and found significant weight gain in SAM children. Several studies also showed that supplementation of 50-150 mg/kg/day in 3-4 divided doses was effective in increasing the rate of weight gain. Therefore, we have designed our study to give 100mg/kg/day in 3 divided doses. We think it will be sufficient to replete the deficiency (5, 26).

Comment: “Correction for baseline carnitine levels may be indicated in the final analysis but understanding the distribution of those baseline levels will also be a valuable addition to our current knowledge.”

Response: Thank you sir for your valuable opinion. Yes, we will also try to understand the distribution of baseline carnitine level.

Comment: “In terms of the secondary outcome of study of Levocarnitine’s effect on EED, the interval of 15 days may be too short to recognize an effect on certain biomarkers. Specifically, those of gut permeability may take longer to correct.”

Response: Thank you sir for your valuable guidance and suggestion. In our study design we have a plan to collect sample for EED biomarkers for reassessment at day 15, after completion of intervention. We don’t know whether 15 days or 30 days are adequate to test faecal biomarkers. There is no data on the effect of carnitine supplementation on EED biomarkers. If we wait for 30 days to collect the samples, there would be also a chance of increasing the drop out rate. Because most of the caregivers would not allow their children to stay for such a long time in hospital. It is not feasible as well to visit their homes to collect biological samples. Therefore, we will collect samples and measure EED biomarkers at the end of intervention. Since it is the first study of its kind, we would find evidence whether 15 days are adequate or not.

Comment: “Also, the degree of baseline elevation in inflammatory biomarkers (including enteric inflammation) may be dependent on the type of pathogen causing the diarrhea that led to the child’s admission. Children with secretory diarrhea will have less elevation than those with inflammatory pathogens such as Campylobacter or Shigella. Inflammatory biomarkers to these pathogens may decrease regardless of intervention as the infection clears although likely will not normalize. One way to create a more heterogenous group without expensive pathogen testing would be to exclude children with fecal RBC positivity. Although pathogens such as Campylobacter are increasingly being recognized causing non-bloody diarrhea in addition to the more classic bloody diarrhea, this may help in excluding children with the highest levels of colitis (i.e. those that would lead to fecal RBC testing being positive). Alternatively, if the budget allows, fecal pathogen testing could be arranged and only children with viral disease enrolled as it would be expected that viral pathogens change the inflammatory biomarkers to a lesser degree. Of course, co-pathogen carriage may make screening difficult.”

Response: Thank you sir for your valuable advice. We will enrol the children and collect the base line samples when the acute phase will be managed and the study participants will be shifted to NRU for rehabilitation. We anticipate that diarrhoea would be resolved during the time of enrolment. Hence, we expect that the role of pathogens would be subsided. Moreover, our budget would not allow us to collect additional samples and perform culture and occult blood test. Therefore, we will not do culture or occult blood test in this study.

Comment: “Finally, there is evidence that the enteric microbiota plays an important role in carnitine metabolism. While likely beyond the scope of this project and budget, it would be reasonable to bank a separate aliquot of stool for the purpose of future microbiome studies. If this trial does demonstrate an effect in the treatment group, external funding for this line of question could potentially be secured. This should be a separate aliquot to limit freeze-thaw cycles and be stored in RNase/DNase free cryovials at -80oC.”

Response: Thank you sir for your valuable suggestion. We included the idea in our plan, and we will preserve the sample for future microbiome studies. (Please see page- 6)

External Reviewer: 2

Page 1 of 2

**Title:** Role of L-Carnitine supplementation on rate of weight gain and biomarkers of Environmental Enteric Dysfunction (EED) in children with severe acute malnutrition

Summary of Referee’s Opinions: Please see the following table to evaluate the various aspects of the proposal by checking the appropriate boxes. Your detailed comments are sought on a separate, attached page.

|  | Rank Score | | |
| --- | --- | --- | --- |
|  | High | Medium | Low |
| Quality of project |  | √ |  |
| Adequacy of project design | √ |  |  |
| Suitability of methodology | √ |  |  |
| Feasibility within time period | √ |  |  |
| Appropriateness of budget | No idea |  |  |
| Potential value of field of knowledge |  | √ |  |

